### **6.4 Secondary endpoints**

The secondary endpoints are the following:

- Measurement of IL-6 and HMGB1 T0 i.e. patient inclusion, at T24 hours, T48 hours, and T 72 hours after treatment initiation;
- Routine measurements of norepinephrine dose, inotropic score, and vasopressor dependency index T0, T24, T48 and T72;
- Haemodynamics: MAP, CVP, HR, CO, ELWI, PVPI T0, T24, T48 and T72
- Routine measurements of volume requirement T0, T24, T48 and T72;
- Routine measurements of ventilation parameters PO2/FiO2, SvO2 T0, T24, T48 and T72;
- Urine output (ml/d)
- Lactate, procalcitonin and pH measurements at T0, T24, T48 and T72 after treatment initiation;
- SOFA score calculation at T0, T24, T48 and T72 ;
- Incidence of renal failure, ICU length of stay
- Patient survival at D28;
- Recording of AEs/SAEs

## **7 Design of the clinical investigation**

The clinical study design is the following: Pilot,  
Proof of concept,  
Prospective, Open,  
Multi-centre,  
Randomized,  
Controlled trial between three parallel groups

The study is open as the standard of care of septic shock treatment does not include extracorporeal support.

## 7.1 Study duration

The study is planned to start 01/08/2013 (First patient in) and stop in 01/02/2017 (Last patient out). The patient enrolment is expected to last 3 years and 6 months.

## 7.2 Extracorporeal devices

### 7.2.1 The oXiris™ device

The product name is oXiris™ Set, which consists of the following:

- a heparin grafted hollow fibre haemofilter/dialyzer
- a tubing circuit
- a cartridge plate
- an effluent bag (5 Litres)

The hemodiafilter is comprised of a hollow fibre membrane with an effective surface area of 1.5m^2. This hollow fibre membrane is composed of:

- a co-polymer of Acrylonitrile and sodium methallyl sulfonate (AN69)
- a surface treatment agent: Polyethyleneimine
- Heparin that is grafted to the membrane

The oXiris™ Set is sterilized by Ethylene Oxide.

The oXiris™ Set is intended for use only with the PRISMAFLEX Control Unit equipped with software version 4.00 or later in providing continuous fluid management and renal replacement therapies.

#### oXiris™ indications and contraindication

The oXiris™ set is intended for use in the following veno-venous therapies: CVVH, CVVHD, CVVHDF. This product is CE marked for the intended use described below and manufactured according to the essential requirements described in the directive 2007/47/EEC and it belongs to Class III device according to this directive.

The system (oXiris™ and Prismaflex) is intended for patients who have acute renal failure, fluid overload or both.

The oXiris™ set is currently not intended for the use in patients with septic shock without acute renal failure.

All information related to manufacturing of study product is available in the Investigator's brochure.

oXiris™ is contra-indicated for patients who have a known allergy to heparin or Heparin Induced Thrombocytopenia (HIT).

#### oXiris™ labelling

Each investigational device will bear the following information:

- Identification label bearing all mandatory and regulatory information, including sterilization and shelf life;
- Barcode label for product manufacturing traceability purposes.

A label stating "for investigational purpose only" will be affixed to each box.

The solutions used to perform CRRT will be Gambro Bicarbonate fluids such as Hemosol B0, PrismaSol 2, PrismaSol 4, and Phoxilium.

### **7.2.2 The Toraymyxin™ device**

Toraymyxin™ (PMX; Toray, Tokyo, Japan) is a cartridge selectively removing blood endotoxin. It consists of the following:

- A polycarbonate case containing a fibre composite tissue based on polystyrene,
- immobilized polymyxin B through a covalent binding,
- a tubing circuit.

The blood flows radially and homogeneously from a central pipe with holes in its sidewall to the composite fibre fabric wound around it.

It is well known that polymyxin-B antibiotic binds endotoxin and has bactericidal activity. Polymyxin-B has a strong affinity to endotoxin and is able to bind the lipid A portion of endotoxin through ionic and hydrophobic interactions. Intravenous injection of polymyxin-B has significant nephrotoxic and neurotoxic effects. However, covalently immobilized polymyxin-B on the adsorbents of PMX does not leak out into the blood stream, thus allowing the clinical application without the known toxic effects of polymyxin-B.

#### *Toraymyxin™ indications and contraindications*

Toraymyxin™ is intended for endotoxin removal in patients with severe sepsis and septic shock. Toraymyxin™ has been CE-marked according to ECC 93/42 for medical devices since 1998. It has been used in Japan for over 15 years with more than 70,000 patients treated so far.

The parenteral application of polymyxin B is limited by its toxicity.

### **7.3 Device accountability**

The study products intended for the clinical study must be stored in a safe place with restricted access and used only to treat the patients included in the study under the sole supervision of the investigator. The principal investigator (or delegated person) is responsible for recording both the product supplied as well as the number of product units used during the study, in addition to material.

The principal investigator is solely responsible for keeping records of updated documents according to the following requirements:

- a) The date of receipt;
- b) Identification of each investigational device (batch number);
- c) The expiry date;
- d) The date or dates of use;
- e) Subject identification;
- f) Date on which the investigational device was returned/withdrawn from subject, if applicable;
- g) The date of return of unused, expired or malfunctioning investigational devices, if applicable.

At each visit, the Study Monitor must ensure that products have been duly counted, and that the products are being used according to their specifications.

### **7.4 Study population**

#### **7.4.1 Inclusion Criteria**

The following inclusion criteria should be fulfilled at the time of enrollment within 24h of suspected septic shock.

Patients with septic shock, defined as: persistent catecholamine dependency with a vasopressor index > 3 after fluid resuscitation with at least 30ml/kg of i.v. fluid administered

prior to time of randomization, and at least ONE of the following criteria: metabolic acidosis, neurologic dysfunction (GCS  $\leq 14$ ), renal dysfunction, (RIFLE Class Injury or Failure), or hepatic dysfunction (Transaminases  $\geq$  twice upper limit of normal).

- Male and Female patients  $\geq 18$  years
- Endotoxin levels  $\geq 0.6$  IU within 24h from the time of suspected septic shock. If the first Endotoxin level is  $\geq 0.4 \leq 0.6$  IU EAA, the measurement should be repeated 2-3 times within the screening period of 24 hours.

#### **7.4.2 Exclusion Criteria**

The presence of any one of the following exclusion criteria will lead to exclusion of the subject:

Contraindications on ethical grounds

Endotoxin levels  $< 0.6$  IU EAA Pregnancy

or breast feeding

Neutropenia (circulating neutrophils  $< 500/\mu\text{l}$ )

Immune-suppressive therapy or Steroid medication  $\geq 30\text{mg/d}$  Prednisone Equivalent

Use of Vasopressin (Pitressin)

Organ transplantation within the last 12 months Terminally

ill patients classified as “do not resuscitate” Have active

bleeding or are at increased risk for bleeding

- Have a platelets count after substitution  $> 30$  G/L
- Have an INR  $> 4$
- Substitution of more than 2 erythrocyte concentrate within 6 hours

History of sensitivity to polymyxin B or to anticoagulant (heparin) HIT or allergy to heparin

Need for extracorporeal membrane oxygenation (ECMO)

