| Diagnosis and Inclusion Criteria: | 
 
Patients with septic shock, defined as: persistent catecholamine dependency with a vasopressor index > 3 after fluid resuscitation with at least 30ml/kg/KG prior to time of randomisation, and at least ONE of the following criteria: metabolic acidosis, neurologic dysfunction (GCS ≤ 14), renal dysfunction (RIFLE Classification: staging Injury or Failure) or hepatic dysfunction (Transaminase ≥ twice upper limit of normal).
 
Male and Female patients ≥18 years
 
Endotoxin levels ≥0.6 IU EAA within 24h from the time of suspected septic shock. If the first Endotoxin level is <math>0.4 \leq 0.6</math> IU EAA, the measurement should be repeated 2 -3 times within the screening period of 24 hours..
 
                                                                                               |
| Exclusion Criteria:               | 
 
Contraindications on ethical grounds
 
Endotoxin levels <0.6 IU EAA
 
Pregnancy or breast feeding
 
Neutropenia (circulating neutrophils <500/μl)
 
Immune-suppressive therapy or Steroid medication ≥30mg/d Prednisone Equivalent
 
Use of Vasopressin (Pitressin )
 
Organ transplantation within the last 12 months
 
Terminally ill patients classified as “do not resuscitate”
 
Have active bleeding or are at increased risk for bleeding, defined as platelets count after substitution >30 G/L; INR >4; and at least Substitution of more than 2 erythrocyte concentrate within 6 hours
 
History of sensitivity to polymyxin B or to anticoagulant (heparin) HIT or allergy to heparin
 
Need for extracorporeal membrane oxygenation (ECMO)
 
 |

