The rationale of the extracorporeal therapy with PMX is to remove circulating endotoxin by adsorption, thus preventing progression of the biological cascade of sepsis. Overall, nine randomized controlled trials (mainly published in Japan) investigated the PMX on outcomes (blood pressure, the use of vasoactive drugs mortality and endotoxin levels) (18-24).

Endotoxin concentrations decreased after PMX treatment in most of the studies, but did not significantly change in the European randomized controlled trial (25). A recent review reported similar adverse events, including clotting of the device when compared to CRRT

(16). Especially no adverse events indicative of nephrotoxicity and neurotoxicity were reported in a recent review (16).

The following is a list of problems that could be theoretically encountered with the use of extracorporeal blood purification treatments:

- Circuit and filter thrombosis, possibly leading to blood loss;
- Heparin-associated bleeding or heparin-induced thrombocytopenia;
- Hemodynamic instability, mainly due to hypovolemia;
- Various catheter-related complications, including inadvertent arterial puncture, local bleeding, hematoma, pneumothorax, haemothorax, retroperitoneal bleeding or cardiac arrhythmia, thrombosis, infection, mechanical problems (e.g. malpositioning);
- Electrolyte disturbances;
- Undesired losses of water-soluble compounds, including drugs and trace elements.

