### **7.5 Subject Recruitment**

Patients who met all inclusion criteria and none of the exclusion criteria (see above) will be considered for enrolment. Informed Consent will be obtained as described in section 12.3.

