### **7.6.3 oXiris™ treatment group**

#### Vascular access

In the oXiris™ group, patients will receive extracorporeal therapy over a venous double-lumen catheter, inserted through the jugular, subclavian or femoral vein. The catheter will be inserted by a trained physician according the guidelines for performing ultrasound guided vascular cannulation (28).

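### The platelet limit in the bleeding-risk exclusion points the wrong way in both section 7.4.2 and the synopsis, and the link between its three conditions is unclear

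*Protocol*

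**What the plan says.** Section 7.4.2 opens its list with "The presence of any one of the following exclusion criteria will lead to exclusion of the subject". One entry covers patients who have active "bleeding or are at increased risk for bleeding". Three bullets follow with no linking word between them:

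- "Have a platelets count after substitution $> 30$ G/L"
- an INR above 4
- transfusion of more than two erythrocyte concentrates within 6 hours

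The synopsis presents the same three items as the definition of increased risk: "Have active bleeding or are at increased risk for bleeding, defined as platelets count after substitution" above 30 G/L, then INR above 4, then "and at least Substitution of more than 2 erythrocyte concentrate within 6 hours".

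Section 7.5 makes the list binding: "Patients who met all inclusion criteria and none of the exclusion criteria (see above) will be considered for enrolment". Section 10 forbids departures from the plan except in emergencies, and section 14.1 has the monitor verify compliance with the eligibility criteria.

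**The concern.** A higher platelet count does not mark a higher risk of bleeding, so the platelet bullet contradicts the heading it stands under. As written, it can never pick out the severely thrombocytopenic patient whom the heading is meant to protect.

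The threshold matters because of the treatment. In both device arms "patients will receive extracorporeal therapy over a venous double-lumen catheter, inserted through the jugular, subclavian or femoral vein" (sections 7.6.3 and 7.6.4). Both circuits are primed with heparin, and heparin is the usual circuit anticoagulant. Section 5.1.3 names "Heparin-associated bleeding or heparin-induced thrombocytopenia" and local bleeding at the catheter among the foreseeable problems.

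A second, smaller defect is that the link between the three conditions is not settled. Section 7.4.2 gives none of its own, and its lead-in is not stated to reach down to the sub-bullets. The synopsis wording can mean all three together, or platelets or INR combined with transfusion. These rules exclude different patients.

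**Working it through.** The protocol gives no figure to reproduce here, so the check is one of wording and logic.

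**Direction.** Three comparisons within the protocol agree:

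1. Section 7.4.2 and the synopsis both print the platelet limit as greater than 30 G/L. The sign survives in two separately formatted places, so a text-extraction fault is unlikely.
2. The INR limit in the same list points correctly in both places: a higher INR means a higher risk.
3. The SOFA table in section 7.8.3.2 scores coagulation as worse when platelets fall.

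No other section states a platelet limit for exclusion.

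**Does any link between the conditions rescue the rule?** Classify a patient by three yes/no conditions: L = platelets below 30 G/L after substitution, I = INR above 4, R = more than two concentrates in 6 hours. This gives 2 × 2 × 2 = 8 patterns, 4 of them with low platelets. Active bleeding, exclusion by judgement and a count of exactly 30 G/L are set aside. The written rule uses not-L as its platelet term; the corrected rule uses L. The link is held fixed and only the sign is turned.

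- *Any one.* Written: not-L or I or R. Only L with neither I nor R escapes, so 8 − 1 = 7 patterns are excluded. Corrected: L or I or R. Only the pattern with none of the three escapes, again 7.
- *All three.* Written: not-L and I and R, 1 pattern. Corrected: L and I and R, 1 pattern.
- *(Platelets or INR) and transfusion.* Written: (not-L or I) and R. Of the 4 patterns with R, only L without I escapes, so 3 are excluded. Corrected: (L or I) and R, again 3.

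| Link | Excluded, written | Excluded, corrected | Low-platelet patterns excluded, written | Low-platelet patterns excluded, corrected | Patterns that change |
|---|---|---|---|---|---|
| Any one | 7 of 8 | 7 of 8 | 3 of 4 | 4 of 4 | 2 |
| All three | 1 of 8 | 1 of 8 | 0 of 4 | 1 of 4 | 2 |
| (Platelets or INR) and transfusion | 3 of 8 | 3 of 8 | 1 of 4 | 2 of 4 | 2 |

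The two patterns that change are always one matched pair, in which INR and transfusion are the same and platelets decide. In that pair the written rule excludes the patient above 30 G/L and admits the one below.

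Two illustrations with assumed values:

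- Under *any one*, a patient with platelets of 200 G/L, a normal INR and no transfusion is excluded. The same patient at 10 G/L is not.
- Under *all three*, a patient with platelets of 10 G/L, INR 5 and three concentrates is not excluded. The same patient at 200 G/L is.

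The equal totals before and after follow from the structure of the rule. The patterns carry no frequencies, because the protocol gives none, so the table shows which patients are misclassified and not how many.

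**The case against.** The best case against giving this weight is that the slip is obvious. It stands under a bleeding-risk heading beside a correct INR limit. Applied literally, with each bullet excluding alone, it would bar almost everyone, so clinicians will probably have read it as intended. The sentence that every patient above 30 G/L is excluded holds only under that reading; under the other two, transfusion is also required and the sign decides fewer cases.

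There are also safeguards. The parent line in section 7.4.2 is an exclusion ground in its own right, so a thrombocytopenic patient can be kept out on judgement. Sections 7.6.3 and 7.6.4 omit circuit anticoagulant when bleeding risk is high, and 7.6.3 offers a heparin-free rinse. Sections 7.5.1 and 12.3 allow withdrawal or alternative treatment later. This is version 1.7 of 16.06.2016, with the last patient due out on 01/02/2017, so most of the planned period had passed.

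All of this is fair, and it limits the likely harm. It does not remove the error. The safeguards depend on individual judgement or act only after enrolment, and omitting heparin leaves the catheter risk. The synopsis ties increased risk to the faulty list and so closes the judgement route that 7.4.2 leaves open.

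One part of the objection shapes the remedy. Because the protocol gives instructions for treating patients at bleeding risk, it expects some to be enrolled. The widest exclusion should therefore not be assumed to be the intended one.

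**Conclusion.** The platelet condition is wrong as written in both places, and the finding does not depend on which of the three links was meant. The unclear link is a genuine but secondary defect.

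The consequence is confined to eligibility and safety. The protocol does not reveal how sites applied the line. If each bullet excludes alone, enrolling an ordinary patient above 30 G/L departs from the text, whereas excluding one below 30 G/L does not, because the parent line of 7.4.2 permits it.

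The conclusion rests on one inference: that the limit was meant to catch low counts. The heading supports it, but the protocol nowhere prints the limit in that direction. Because this is an operative safety threshold and costs almost nothing to correct, it should be corrected.

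**What to change.** Change the platelet condition to below 30 G/L in section 7.4.2 and in the synopsis. Have the clinical leads confirm two things:

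- **The cut-off**, including how a count of exactly 30 G/L is treated.
- **The link between platelets, INR and transfusion.** Letting any one suffice is the most protective choice, but it excludes more patients than the synopsis wording does.

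Put the same confirmed sentence in section 7.4.2, the synopsis and any eligibility checklist in use. Then check the records of enrolled patients for counts below 30 G/L after substitution at enrolment.

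The cost is a short amendment, one sign and one linking phrase in two places, and a look at one laboratory value in the 30 planned patients plus replacements. Turning the sign alone loses no patient whom the heading meant to include. If the leads decide that any one condition suffices, some candidates with only a raised INR or only the transfusion criterion would also be screened out.

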### **7.5 Subject Recruitment**

Patients who met all inclusion criteria and none of the exclusion criteria (see above) will be considered for enrolment. Informed Consent will be obtained as described in section 12.3.

#### **7.5.1 Withdrawal Criteria**

Patients are free to withdraw from the study at any time without having to justify their decision. When a patient decides to withdraw from a study, he/she will be systematically contacted and given the opportunity to provide information about the reason(s) of his/her withdrawal and possible occurrence of an adverse event.

If at any time the investigator considers that malfunctions/AEs could possibly have led to a deficiency in the patient's treatment, the treatment in question shall be discontinued and replaced by a standard treatment.

Patients must be withdrawn from the study if any of the following occurs:

- Any event which, in the opinion of the investigator, may either endanger the health of the patient, or may adversely influence the result of the study;
- Patients refusing or not considered capable, as judged by the investigator, of following instructions of the study;
- In case of clotting of three oXiris™ circuits within 24 hours, or a filter downtime for more than 6 hours, the treatment will be stopped.
- The need for extracorporeal membrane oxygenation (ECMO)
- Patients who die within 72 hours from admission

Withdrawn patients after randomization will be replaced. The reason for withdrawal should be recorded in the Case Report Form (CRF).

If withdrawal is related to the possible occurrence of adverse events, the patient will be followed up according to the adverse event procedure.

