| Number of Subjects: | 30 patients in total                                                                                                                                                                                                                                                                                                                                                                                                                                                                                                                                                                                                                                                                                                                                                                                                                                                                                                                                                                                                                                                                                                                                                                                                                                                                                                                                                                                                                                                                                                                                                                                                                                |

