## **7.7 Assignment to study treatment**

#### **Randomization**

All eligible patients will be randomly assign to either conventional SOC treatment according to the Surviving Sepsis Campaign Guidelines (27), or SOC treatment with oXiris™ hemofiltration, or SOC treatment with Toraymyxin™ hemoperfusion within 24 hours of admission to the ICU. Patients will be distributed into these 3 groups, in accordance with the randomization table kept in the investigator's office. The randomization list will be performed using a computer generated (simple random number) scheme.

The allocation sequence is concealed in sealed envelopes held at the study centre, which is available 24 hours a day.

According to paragraph 7.5.1 withdrawn patients will be replaced in order to analyse 10 patients per group.

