After the subject has entered the study the clinician remains free to give alternative treatment to that specified in the CIP at any stage if he/she feels it is in the subject's best interest, but the reasons for doing so should be recorded. In these cases, the subject remains within the study for the purposes of follow-up and data analysis. All subjects are free to withdraw at any time from the CIP treatment without giving reasons and without prejudicing further treatment.

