## **13 Statistical considerations**

As mentioned, the endotoxin activity is not well described in the literature, which makes a sample calculation difficult. Therefore, this trial was designed as a pilot study analysing 30 patients in order to collect data enabling an accurate design of future investigations. Dependent and independent continuous variables will be compared using Wilcoxon and Mann-Whitney, respectively. In cases of serial measures repeated measures statistics will be applied. For multiple comparisons overall tests will be used: ANOVA for continuous variables and Kruskal-Wallis tests for ordinal scaled variables. Categorical data will be compared using Fisher's exact and  $\chi^2$  test. The normal distribution of study variables will be confirmed using Kolmogorov-Smirnov test. A P value < 0.05 will be considered statistically significant. To obtain adjusted differences in outcomes for the two study populations, logistic regression will be performed to control for factors or confounders that are significantly different ( $p < 0.05$ ) between compared groups. Data will be analysed using the Statistical Package for Social Sciences (SPSS Windows, version 19.0; SPSS Inc., Chicago, IL).

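### Section 7.5.1 withdraws and replaces randomised patients on the unblinded investigator's opinion that an event may affect the study result or endanger health, which permits selection after allocation is known

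*Protocol*

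**What the plan says.** Protocol section 7.5.1 introduces its list of withdrawal criteria with "Patients must be withdrawn from the study if any of the following occurs". The first item is any event that, "in the opinion of the investigator, may either endanger the health of the patient, or may adversely influence the result of the study". The event is not defined further, and no independent or blinded review of the decision is named. The section continues: "Withdrawn patients after randomization will be replaced". The reason is to be recorded in the CRF, and withdrawals linked to adverse events are followed up under the adverse event procedure.

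Section 7.7 gives the purpose of replacement: "withdrawn patients will be replaced in order to analyse 10 patients per group". The synopsis sets the size at "30 patients in total", and section 13 describes a "pilot study analysing 30 patients in order to collect data enabling an accurate design of future investigations".

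On blinding, section 7 states: "The study is open as the standard of care of septic shock treatment does not include extracorporeal support".

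Two other places treat similar situations differently. An earlier paragraph of 7.5.1 deals with malfunctions or adverse events that may have made the patient's treatment deficient: the treatment is discontinued and standard treatment given, with no mention of leaving the study. Section 12.3 lets the clinician give alternative treatment at any stage and adds: "In these cases, the subject remains within the study for the purposes of follow-up and data analysis".

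**The concern.** The decision to remove a patient rests on opinion, is triggered by a mere possibility, and is made by someone who knows the allocation. That person may also know how the patient is doing. Under 7.8.2.1 endotoxin activity (EAA) is measured at treatment start and at 24, 48 and 72 hours, and 7.8.3.1 has these samples analysed at once rather than stored. Section 7.9.3 records lactate, catecholamine doses and SOFA at 24 and 48 hours. Information related to the 72-hour primary endpoint can therefore exist before that endpoint is measured.

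One limb of the criterion refers to the effect on the study's result. The other turns an event that may endanger health into exit from the study and replacement, although stopping the study treatment and continuing to observe the patient are separable. Both limbs can take patients with a poor course out of the analysed 10 and put new patients in their place. Randomisation no longer protects the comparison if this happens at different rates, or for different reasons, in the three arms.

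It matters in a pilot too. The data are meant to support the design of later trials, so a distorted effect estimate or spread would carry forward. Section 13 also tests at P < 0.05.

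**Working it through.** **Planned size.** 3 groups × 10 analysed patients (7.7) = 30, which agrees with the synopsis and section 13. The protocol gives no power, effect size or SD, so there is no sample size calculation to reproduce.

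**The rules side by side.**
- Trigger: an event with a possible effect on the result or on health, judged by the investigator (7.5.1).
- Knowledge of arm: yes (section 7).
- Consequence: exit from the study and replacement (7.5.1), so that 10 per group are analysed (7.7).
- Data after exit: only adverse event follow-up is mentioned, and only for withdrawals related to adverse events (7.5.1).
- Contrast: alternative treatment means staying in follow-up and analysis (12.3). Deficient treatment means a change of treatment, with exit not mentioned (7.5.1).

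A patient whose device treatment is stopped after an adverse event could fall under any of the three rules. Under one the patient is replaced, and under another analysed.

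**Illustration of size.** Inputs from the protocol: 10 per arm, two arms compared by Mann-Whitney, P < 0.05. Assumptions: no true effect, normally distributed 72-hour EAA with higher values worse, two-sided exact test, and k = 1, 2 or 3 patients in one arm only replaced by new random patients. The protocol gives no basis for k.

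*Baseline.* For 10 versus 10 the exact test rejects at U ≤ 23 or U ≥ 77. Each tail has probability 2.2%, so without swaps 2.2% of null trials falsely favour a given arm.

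*Shift of the arm mean.* The three largest of 10 standard normal values have expected sizes of about 1.54, 1.00 and 0.66. Replacing the k worst by new patients with mean 0 shifts the arm by:
- k = 1: 1.54/10 = 0.15 SD
- k = 2: (1.54 + 1.00)/10 = 0.25 SD
- k = 3: (1.54 + 1.00 + 0.66)/10 = 0.32 SD

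If patients are chosen on a trigger that correlates r with the 72-hour value, each shift is multiplied by r. For k = 1 that is 0.3 × 0.154 = 0.05 SD or 0.5 × 0.154 = 0.08 SD. For k = 3 it is 0.3 × 0.32 = 0.10 SD or 0.5 × 0.32 = 0.16 SD.

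*False results favouring that arm* (simulated, error roughly 0.1 to 0.2 percentage points):

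| Who is swapped | k = 1 | k = 2 | k = 3 |
|---|---|---|---|
| Trigger correlates 0.3 with 72-hour EAA | 2.7% | 3.2% | 3.5% |
| Trigger correlates 0.5 | 3.2% | 4.0% | 4.8% |
| Random members of the worse half | 3.0% | 4.2% | 6.0% |
| The worst 72-hour values themselves | 4.9% | 7.9% | 10.5% |

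The last row is an upper bound. The 72-hour sample is the final EAA measurement, so a withdrawal before 72 hours cannot act on its value. If the same rule works equally in both arms at r = 0.5, the two-sided error is 4.6-4.9%, so the distortion comes from unequal use between arms.

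**The case against.** The best defence is that the clause is standard wording aimed at events that compromise validity, not at poor outcomes. That may well be the intention, but the text does not confine it to such events, and use in good faith would still select patients after allocation is known. It is also fair to say that this is a pilot without a power claim, that reasons for withdrawal are recorded, and that adverse events are collected to day 28. These make removals visible but do not put the patients back into the comparison.

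Several stronger readings are tempting and are not supported:
- *That unfavourable results will be removed.* The rule permits this. Nothing shows that it is intended or will occur.
- *That circuit-related events can arise only in the device arms.* Section 7.6.5 provides CRRT whatever the allocation, 7.9.3 records renal replacement in the standard-care group, and 5.1.3 estimates that about 50% of patients with severe sepsis eventually need it. An imbalance is plausible because device patients are assigned a circuit, but exclusivity is wrong.
- *That 12.3 states the opposite of 7.5.1.* Its trigger is a clinician giving alternative treatment. The two rules overlap and conflict only where a case falls under both.
- *That no analysis could repair the damage.* The protocol defines no analysis set and does not say that withdrawn patients' data are discarded. Their absence from the analysed 10 is inferred from the replacement rule in 7.7. What can be said is that 7.5.1 does not provide for further EAA samples after withdrawal, so those values may not exist.

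**Conclusion.** The point stands as a flaw in a stated rule. An open trial withdraws and replaces randomised patients on the investigator's opinion about the study's result or a danger to health, and fills the groups to 10 for analysis. This permits selection related to prognosis or emerging outcome, and it has to be reconciled with 12.3 and with the treatment-only paragraph of 7.5.1.

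The conclusion rests on the text and not on the simulation. With 1 to 3 of 10 patients swapped in one arm and a moderately correlated trigger, favourable false positives go from 2.2% to about 3-5%. The 5-10% range, with shifts of 0.15-0.32 SD, belongs only to the worst case. The number of swaps, the correlation and the one-sided use are all assumptions, so these figures show direction and order of size and are not a forecast.

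**What to change.** 1. In the first withdrawal criterion of 7.5.1, delete the limb about influence on the result of the study.
2. Add that a patient whose study treatment is stopped because of an event under this criterion remains in the study for EAA at 24 to 72 hours, day-28 outcome and safety follow-up, is analysed as randomised and is not replaced. Adjust the replacement sentences in 7.5.1 and 7.7 to match.
3. Reconcile 7.5.1 with 12.3, and with the paragraph of 7.5.1 that only discontinues treatment, so that one event leads to one study status.

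The change concerns study status and analysis only. When treatment is stopped remains as the protocol has it, and the other withdrawal criteria are not part of this point. The cost is a short amendment. The downside is small: patients with shortened treatment stay in the analysis and may dilute the estimated effect.
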